#### Follow-up assessments of self-management

Formal follow-up sessions will be undertaken either via telehealth, in person, or by phone (or email if everything else is not possible) at 3, 6, and 12 months. Face-to-face follow-up sessions, where possible, will be planned to coincide with regular hospital outpatient visits. Telehealth, phone, or email follow-up will be conducted at a mutually agreed time between the healthcare professional and the patient. Measures of illness control, unplanned hospital visits, and questionnaires will be collected at interval periods as indicated in Table 1 using EMR to reduce reporter burden. The focus of follow-up sessions is to review the participant’s progress and provide coaching to achieve their agreed goals and/or set new goals as needed. The health professionals act as a resource person, providing motivation and assisting with problem solving as necessary. Follow-up sessions will follow the same structure as the initial face-to-face session and dependent on the goals of the young person. At 3 months, participants are given a reminder about the booster session which is scheduled at 6 months and their contact details confirmed.

#### Standard care procedures

The control group will receive standard care which consists of usual care practices which are offered by the adolescent’s individual specialist treating team. In practice, this will be general advice on self-management behaviors to a variable degree and frequency. Participants in the control group will be provided with a general information brochure after randomization providing encouragement for participants to think about the concept and goals of self-management. Initial control participants will be advised that they will be contacted to start the program in 6 months’ time. Control participants will be contacted by a member of the research team via phone, 1 month prior to the commencement of the program to advise of the start date which will be coordinated to coincide with the participant’s next clinic visit. The sole purpose of this call is to provide participants with the planned program start date, no intervention work will be provided during this call.

### Criteria for discontinuing or modifying allocated interventions {11b}

The data collected at each assessment point will be used to determine and monitor the safety of the trial participants and to determine if any modifications to the trial protocol are required. A concurrent implementation process will be conducted, and allocated study interventions for trial participants may be modified or discontinued in response to the participant’s request, worsening of disease, or harms. Any changes or modification of the trial protocol will be reflected in the study protocol and the Australian, New Zealand Clinical Trials Registry (ANZCT).

### Strategies to improve adherence to interventions {11c}

Strategies to improve adherence to interventions and maintain engagement are implemented in the study. Participants in the intervention group will receive a maximum of 3 phone calls, spaced 3-weekly and a booster session scheduled at 6 months delivered by a member of the research team. Condition-related data on markers of illness control including laboratory measurements will be obtained from the participants’ EMR.

Participants will also be provided with a confirmation of appointment letter which will be sent via mail or email depending on the participant’s preference prior to each follow-up appointment to maintain adherence to the program, which is consistent with Departmental practice. For participants who have missed a follow-up appointment, a member of the research team will call the participant to reschedule the appointment within a 1-week period if possible. Appointments will be offered via telehealth, phone, or face-to-face consultation. Where possible, face-to-face self-management appointments will be scheduled to coincide with other routine hospital visits to improve attendance, participation, and adherence to the intervention.

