#### Follow-up data collection

Adherence to prescribed treatment regimenBaseline observations will be collected from both the waitlist control group and the intervention group before randomization. Potential participants in the intervention group will be contacted via phone by a member of the research team. Follow-up of participants in the intervention group will be undertaken by a member of the research team via phone or telehealth (depending on the young person’s preference) at 3, 6, and 12 months to follow-up on adherence to the prescribed treatment post intervention. Participants who do not respond to 3 attempts to contact them at any time point will be treated as missing data.

Information from the participants will be obtained by completing the PIH scale via a semi-structured interview. Subsequently, participants allocated to the wait list control group will be contacted by phone by a member of the research team and provided with a self-management information brochure, with no further contact from the research team. At 6 months, participants in the waitlist control group will be contacted by phone by a member of the research team and invited to participate in the intervention as described for the initial intervention group.(b)Markers of illness control and unplanned hospital visits

The research team will obtain standard measures of illness control for all participants who have been recruited into the study and who have consented to clinical information being obtained for research purposes. The control of chronic illness is the best quantitative measure of therapy adherence that is available. This will be undertaken by way of the research team extracting information from the electronic medical records (EMR) and the young person’s primary physician contacted for further information. Data on unplanned hospital visits will be retrieved by the research team from EMR and/or accessed through the young person’s My Health Record if available.

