### Sample size {14}

The primary outcome of a response to treatment is defined by improvement in disease markers listed in Table 1. We estimate that fewer than 15% of participants would show improvement in disease under usual care, and the intervention would only be considered worthwhile implementing if it can improve responses by a substantial margin. A study conducted by Rhee and colleagues, which evaluated the effectiveness of a self-management program for adolescents with asthma, found overall the intervention group reporting greater improvements in outcome measures; knowledge, self-management skills self-efficacy, and Quality of Life (QOL), than the control group [66]. A study of 54 participants (27 per group) will have 80% power at 5% two-sided alpha to detect a difference in response rates between treatment arms if the rate under usual care is 15% or less and the true difference in proportions is at least 35%, using a chi-square test. To allow for some loss to follow-up, we plan to recruit a total of 60 participants. Participants who withdraw from the study will not be replaced as the power analysis allows for attrition. Participants who withdraw from the study, may have their clinical outcomes determined from their medical records to ensure that the results of the research study can be measured accurately.

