## Data collection and management

### Plans for assessment and collection of outcomes {18a}

Patient demographic data will be collected at baseline (see Additional file 3). All data collection questionnaires are programmed in Research Electronic Data Capture (REDCap) and include Partners in Health (PIH) Scale, collected at baseline, 3, 6, and 12 months follow-up. Paediatric Quality of Life Inventory (PedsQL) version 4.0 (Teenage Report); Time Management Questionnaire; Kessler Psychological Distress Scale (K10) collected at baseline, 3 months, and 12 months follow-up. Additional data on makers of illness control and unplanned hospital admissions and emergency department visits will be obtained from the EMR at baseline, 3, 6, and 12 months follow-up. Data questionnaire on feasibility and acceptability will be collected on completion of the study at 12 months (see Additional file 4). Data will be collected and stored in REDCap a secure web-based application used for designing and managing clinical research databases. REDCap is an online data capture tool which stores data in a secure and encrypted manner on the University of Sydney server to which we have access [68]. This research data management platform is a secure web-based software platform used for the data management procedures of this trial including data collection, follow-up, and analyses. The built-in component of REDCap has been pre-prepared to accept only variables within given permissible ranges that are consistent with previous entries before going on to the next section to minimize missing values. Data collection forms pertaining to the study will also be stored in REDCap.

Prior to the commencement of the study, research staff completed the Flinders training workshop conducted over 2 days, by the lead research nurse (JG) who is an Accredited Flinders Trainer. All research staff were assessed as competent against current Flinders competency standards. The training was guided by validated manuals (Accredited Trainer: Flinders Chronic Condition Management Program Manual; The Flinders Chronic Condition Program Participant Manual) with electronic copies of all training resources and PowerPoint presentations available to ensure reproducibility and fidelity of the intervention program.

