### Plans to promote participant retention and complete follow-up {18b}

Participants can withdraw from the study at any time. If the patient decides to withdraw from the study, data collected will be retained as outlined in the consent and the reasons for the withdrawal, if provided, will be recorded for subsequent analysis in the interpretation of results. Participants who withdraw from the study will not be replaced as the power analysis allows for attrition.

In the first 3 months, participants will receive a maximum of 3 phone calls from a member of the research team. In addition, an appointment letter is confirming the details of the next appointment is sent to the participant either electronically or sent in the mail which serves as a reminder of the next scheduled appointment to improve adherence and participation to the intervention.

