### Methods in analysis to handle protocol non-adherence and any statistical methods to handle missing data {20c}

The primary aim of this study is to evaluate the effectiveness of a modified adolescent-friendly version of an adult self-management program within a clinical environment. To allow for some loss to follow-up, we plan to recruit a total of 60 participants. All available data will be analyzed on an intention-to-treat basis, whereby participants are analyzed according to their randomized treatment allocation group, regardless of whether they actually received the intervention, their subsequent withdrawal or deviation from the intervention. There is no intention to impute missing data.

Participants can withdraw from the study at any time. If the patient decides to withdraw from the study, data collected will be retained as outlined in the consent and the reasons for the withdrawal will be recorded for subsequent analysis in the interpretation of results. Participants who withdraw from the study will not be replaced unless attrition is higher than anticipated as we require 30 participants in each group. Participants who withdraw from the study may have their clinical outcomes determined from their medical records to ensure that the results of the research study can be measured accurately.

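### Before crossover, the stated retention measures in effect reach only the intervention arm, and controls have no stated route to the 3-month self-report outcomes the text requires of each group

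*Protocol article*

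**What the plan says.** **Retention measures.** The retention section {18b} sets out withdrawal rules and then names two measures. The first is calls: "In the first 3 months, participants will receive a maximum of 3 phone calls from a member of the research team". The second is a letter confirming the next appointment. The intervention description {11a} and the adherence strategies {11c} assign the calls to the intervention group. Section {11c} says the letters go out before each follow-up appointment, to sustain adherence to the programme. It adds: "For participants who have missed a follow-up appointment, a member of the research team will call the participant to reschedule the appointment".

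**Contact with controls.** Under Follow-up data collection, waitlist controls are phoned and "provided with a self-management information brochure, with no further contact from the research team". They are contacted again at 6 months with the invitation to start. The section on standard care procedures adds a call one month before the start, solely to give the start date.

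**What is to be collected.** Section {18a} lists the "Partners in Health (PIH) Scale, collected at baseline, 3, 6, and 12 months follow-up", and PedsQL, TMQ and K10 at baseline, 3 and 12 months, with no distinction by arm. The secondary-outcome text, the PIH section and the K10 section refer to both groups or each group, with 3 months among the time points.

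**Table 2.** Controls have no assessment of any kind at 3 months. The questionnaire row has the intervention arm at baseline, 3 and 12 months, and controls at baseline, 6, 9 and 18 months. The PIH row has both arms at baseline, 6 and 12 months.

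**Missing data.** Section {20c}: "There is no intention to impute missing data".

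**The concern.** The effort that would bring in outcome data is bundled with the intervention. In the first six months one arm is phoned, written to and rescheduled. The other is to be left alone, so nothing describes how a control would be prompted to complete a questionnaire at 3 months.

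This matters for the second hypothesis (quality of life, self-efficacy, time management, distress). Its scales are self-reported and cannot be recovered later from the medical record. The untreated control period is also short: controls start the programme at 6 months, so a questionnaire missed before then cannot be replaced by one taken after crossover without changing the comparison. If completion depends on arm and non-responders differ from responders, an available-case comparison is no longer protected by randomization.

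**Working it through.** **1. The plan's own figure.** "A study of 54 participants (27 per group) will have 80% power at 5% two-sided alpha" "if the rate under usual care is 15% or less and the true difference in proportions is at least 35%, using a chi-square test" means 15% against 50%, with pooled proportion 0.325.

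n per group = [1.96·√(2·0.325·0.675) + 0.8416·√(0.15·0.85 + 0.50·0.50)]² / 0.35² = 26.9, so 27.

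Power at 27 per group is 80.2%. The stated figure reproduces. "To allow for some loss to follow-up, we plan to recruit a total of 60 participants" implies 54/60 = 90% retained, or 10% loss overall. No loss rate by arm is given. The calculation concerns the primary outcome, which comes from medical records, and the present point does not change it.

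**2. The passages side by side, up to month 6.**

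| Element | Intervention | Control |
|---|---|---|
| Three calls in the first 3 months | Yes, explicit | No |
| Appointment letters, rescheduling calls | Yes | No programme appointment to attach to |
| Other research contact | Follow-up at 3 and 6 months | Brochure call; start-date call at about month 5; invitation at month 6 |
| 3-month self-report, per the text | Required | Required |
| 3-month self-report, per Table 2 | Scheduled | Not scheduled |

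Two contradictions follow. First, the text requires 3-month control questionnaires, while the no-contact rule removes the research team's route to them and Table 2 omits them. Second, the no-contact rule and the start-date call do not agree with each other. In Table 2 the questionnaire row gives the arms no shared time point after baseline. For PIH, month 6 is the only shared one before or at crossover.

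**3. Loss of precision (completion rates and effect size assumed).** Sixty participants at 1:1 give 30 per arm. Assume 90% completion in the intervention arm (27) and 90%, 80%, 70% or 60% in controls (27, 24, 21, 18). The standard error of a mean difference in SD units is √(1/n₁ + 1/n₂). The difference detectable with 80% power is (1.96 + 0.8416) times that. Power is for a two-sided 5% t-test at 0.78 SD, the size that gives about 80% with 27 per arm.

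| Completers (I / C) | Standard error | Detectable difference | Power at 0.78 SD |
|---|---|---|---|
| 27 / 27 | 0.272 | 0.76 SD | 80.3% |
| 27 / 24 | 0.281 | 0.79 SD | 77.8% |
| 27 / 21 | 0.291 | 0.82 SD | 74.7% |
| 27 / 18 | 0.304 | 0.85 SD | 70.7% |

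**4. Bias (non-response and gap assumed).** Let g be the gap between completers and non-completers in SD units, equal in both arms. The bias in the mean difference then has size g × (control share missing − intervention share missing).

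| Control missing (intervention 10%) | g = 0.3 | g = 0.5 |
|---|---|---|
| 20% | 0.03 | 0.05 |
| 30% | 0.06 | 0.10 |
| 40% | 0.09 | 0.15 |

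If g = 0, or if the missing shares are equal, the bias is zero. If non-responders are the worse-off participants, the remaining controls look better than they should and the bias runs against the intervention.

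**The case against.** The strongest reply is that Table 2 explains the silence towards controls: nothing is scheduled for them at 3 months, so missing 3-month control data would be absent by design, not lost through unequal reminders. At month 6, the shared PIH time point, controls are in fact phoned. This largely stands as to mechanism. It does not dispose of the point, because the outcome sections still require 3-month data from each group, and equal reminders alone would not repair the schedule. Even at month 6, intervention participants arrive after calls, letters and a 3-month session.

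A reader might infer that controls have no research contact at all before month 6, or that letters and rescheduling are expressly confined to one arm. Neither is written. There is a brochure call and a start-date call, and the letters and rescheduling are worded for participants generally. Their restriction is an inference from the appointments they attach to, and controls would receive them after crossover.

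A rule that three failed contact attempts make an observation missing is also not limited to one arm, though it follows the text on intervention follow-up. It sets a limit on attempts and does not say who prompts controls, or when.

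A reader might also infer that bias is certain because nothing is imputed. The documents do not support that. They give no missingness by arm, bias needs non-response related to outcome, and the repeated-observation models planned in {20a} can be valid on available data if data are missing at random. Those models cannot, however, supply a control mean at a time point where controls were never asked.

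**Conclusion.** The point holds for the self-reported secondary outcomes (PIH, PedsQL, TMQ, K10) in the period before crossover. The stated retention measures in effect serve one arm, and the no-contact rule and Table 2 both conflict with the sections that call for 3-month data from each group. Followed as written, the no-contact rule leaves the research team no route to those control data. Where control data are collected, lower completion is likely but not established.

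The size is modest under the assumptions shown: power of 71–78% instead of 80% for a 0.78 SD difference, and bias of about 0.03–0.15 SD, or none if non-response is unrelated to outcome. The completion rates, the 0.78 SD and the 0.3–0.5 SD gap are assumptions, not figures from the protocol. The primary outcome and unplanned visits come from records for all participants, possibly even after withdrawal, and are not affected. This should be corrected because hypothesis 2 rests on these scales, but it does not threaten the primary analysis.

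**What to change.** 1. Reconcile Table 2 with the secondary-outcome, PIH, K10 and {18a} text so that both arms have the same questionnaire time points before crossover. The remaining steps do not work without this one.
2. Under Follow-up data collection, limit the no-contact rule for controls to self-management contact, and reconcile it with the start-date call under standard care procedures.
3. At each outcome time point, use the same content-neutral REDCap invitation, the same reminders and the same three contact attempts in both arms, kept separate from programme calls. The letters, calls and rescheduling in {11c} stay as part of the programme.
4. Report questionnaire completion by arm and visit.

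The cost is amendment wording and REDCap set-up; the questionnaires are already programmed there and a three-attempt rule already exists. The downside is that controls receive brief neutral contacts during the waiting period.

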### Relevant concomitant care permitted or prohibited during the trial {11d}

Participants should continue to take medications for other comorbid conditions as prescribed by their primary treating team. Both the intervention and control group will continue to receive medical care by their primary treating team throughout the study. Participants enrolled in the “Adolescent Perx Study,” an investigation into the use and applicability of a self-management app in adolescents with chronic conditions conducted within the SCHN, will be excluded to avoid potential contamination of outcomes in both studies.

### Provisions for post-trial care {30}

Post care trial provisions have been outlined in the young person information sheet. In the event of health care needs arising as a direct consequence of trial participation in relation to emotional distress or psychological upset or discomfort, the participant’s primary treatment team and their parents/carers will be notified. Participants are also advised that they may leave the study at any time. Participants ineligible for inclusion in the current study will be offered the self-management clinic as a standard care option if and when required.

### Outcomes {12}

#### Data collection at baseline

Patient demographic data will be collected in person at baseline and will include the following: age, gender, date of birth, diagnosis, year of diagnosis, ethnicity, current medications and therapy prescribed, and email and contact phone number for both the participant and one parent/caregivers. Consent will also be obtained to collect data measures of illness control from EMR. Demographic and baseline characteristics will be summarized using descriptive statistics.

#### Primary outcome measures

Outcome measures and data collection intervals are summarized in Table 2. The primary outcome measure will be a response to treatment as measured by quantitative condition-specific validated markers of improvement in illness control.

#### Measures of illness control

To clarify our primary outcome measure, we provide here a list (not exhaustive) of the more common conditions seen in specialist care in pediatric hospitals which require significant self-management. These include diabetes, other chronic endocrine conditions, asthma, cystic fibrosis, epilepsy, inflammatory bowel disease, haemoglobinopathies, and inherited metabolic disorders [49]. Measures of illness control can be described as a quantitative measurable parameter including laboratory measurement that can be used to identify clinically meaningful endpoints that can be used to assess the status of a known disease. Common features of chronic conditions include prolonged duration, absence of spontaneous resolution, and a lack of curative therapy, requiring ongoing long-term lifestyle modifications and/or pharmacological treatment to be taken consistently and regularly. These characteristics define the chronicity of each of the conditions that will be assessed as part of the study [50]. An improvement of illness control based on clinical experience, given empirical data are lacking, will be assessed by utilizing predetermined measures of illness control, previously developed in conjunction with specialist teams [51] (Table 1). The proportion in each group who achieve improvement in illness control will be described by number and percentage and the difference expressed as relative risk and confidence interval. Measures of effect will be expressed as relative risk with a decrease of 10% from baseline to 12 months. For any conditions not appearing on this list, we will consult with the referring specialist team to determine the appropriate measure of illness control and what would be clinically considered as an improvement of that particular chronic condition. Improvement of illness control will be defined as sustained improvement in measure of disease control over a 12-month period from baseline as defined in Table 1. Illness control will be defined using a binary notation of which a “yes” or “no” answer will be provided, defined as achieving improvement or not. In many conditions, there will be more than one quantitative measure of illness control. For the purposes of outcome analysis, we have selected the most clinically important marker, but will have data on secondary markers of illness control where relevant.

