^*^Sustained improvement in measure of disease control over a 12-month period from baseline

**Table 2 Tab2:** Schedule of enrolments, interventions, and assessments

Procedure												
**Measure**	**Baseline**		**3 months**		**6 months**		**9 months**		**12 months**		**18 months**	
	**I**	**C**	**I**	**C**	**I**	**C**	**I**	**C**	**I**	**C**	**I**	**C**
Informed consent	**X**	**X**										
Demographic data collection	**X**	**X**										
Measures of illness control	**X**	**X**	**X**		**X**	**X**		**X**	**X**	**X**		**X**
Unplanned hospital visits	**X**	**X**	**X**		**X**	**X**		**X**	**X**	**X**		**X**
Questionnaires	**X**	**X**	**X**			**X**		**X**	**X**			**X**
Partners in Health (PIH) Scale	**X**	**X**	**X**		**X**	**X**		**X**	**X**	**X**		**X**
Feasibility and Acceptability Questionnaire (FAQ)									**X**			**X**
Flinders Program delivery	**X**		**X**		**X**	**X**	**X**	**X**	**X**	**X**		**X**
Booster session					**X**					**X**		

***I*** Intervention (Flinders Program plus usual care), ***C*** Control (waitlist plus usual care)

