### Trial design {8}

This is a pragmatic, two-site, two-arm, parallel, longitudinal randomized controlled trial, using both quantitative and qualitative research methods. Participants are allocated at a ratio 1:1 to the intervention or usual care using a computer-generated random list. An RCT design was chosen for this study due to its accepted applicability in assessing the effects of new healthcare interventions such as a self-management program [37, 38]. This study design has been shown to demonstrate sound methodological evidence [39], and allows for a comparison group at each time period and for analysis between each cluster [37, 40]. The study protocol received approval by The Sydney Children’s Hospitals Network Human Research Ethics Committee, Sydney, Australia. The study protocol has been developed based on the Standard Protocol Items: Recommendations for Interventional Trials (SPIRIT) guidelines Schulz and Grimes [41] (see Additional File 1). Figure 2 demonstrates the flowchart of the study design.

This protocol describes an RCT to demonstrate the efficacy of the Flinders Program™ in adolescents. Following randomization, participants in the intervention group will receive a 12-month nurse-led modified version of the Flinders Program™ plus standard care, while participants in the waitlist control group will receive standard care for 6 months before crossing over to the intervention group until all participants are exposed to the program as demonstrated in the study design diagram in Fig. 1. Given that the data available suggests continuing deterioration without intervention is expected, we consider it ethically responsible to offer the intervention to both participant groups.

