**Fig. 1 Fig1:**
[figure not shown]
CONSORT (Consolidated Standards of Reporting Trials) flowchart for the self-management randomized controlled trial

The study design will include a baseline collection period, followed by sequential, individual randomization to control or intervention. The intervention group and control group will be continually recruited and exposed to the intervention plus standard care and/or standard care with baseline and follow-up observations collected (see “Participant timeline {13}”) until target numbers are achieved (see sample size {14}). All participants will be asked to sign informed consent before the commencement of the study.

This is a pragmatic trial for the following reasons:Our systematic review published in the Journal of Advanced Nursing (2021), provides evidence that self-management programs are effective for adolescents. We have been using the Flinders Program™ clinically for over 5 years with success in demonstrated effectiveness in self-management capacity. What is less well understood is how effective self-management programs remain over time, given the rapid bio-neuro-psychosocial development during adolescence. This study has the capacity to demonstrate duration of effect with 12-month follow-up planned.Given the challenge of recruiting and retaining adolescents in health service research from the clinical experience of the research team and the clear clinical need to intervene [36], the combination of stepped intervention with assessment of duration of effect and guidance on booster sessions appears the more appropriate methodological option.

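### The primary response runs over 12 months, but waitlist controls are offered the program from month 6, so the primary test compares early with delayed program rather than program with usual care

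*Protocol article*

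**What the plan says.** - **Question.** Objectives and hypothesis {7} asks whether the program added to standard care does better than standard care alone.
- **Endpoint.** Under Measures of illness control, the binary primary outcome is fixed as follows: "Improvement of illness control will be defined as sustained improvement in measure of disease control over a 12-month period from baseline". The Table 1 footnote repeats the window: "Sustained improvement in measure of disease control over a 12-month period from baseline". The same section also sets the effect measure over this window: "Measures of effect will be expressed as relative risk with a decrease of 10% from baseline to 12 months".
- **Control arm.** Trial design {8} states: "participants in the waitlist control group will receive standard care for 6 months before crossing over to the intervention group until all participants are exposed". The Intervention description, Follow-up data collection, Standard care procedures and Implementation {16c} sections agree. Table 2 marks program delivery to controls at 6, 9, 12 and 18 months.
- **Analysis.** Statistical methods {20a} compares the number of responders per randomized arm by chi-square test under intention to treat, whatever treatment was received. It names no 6-month primary time point.
- **Sample size.** Sample size {14} gives 27 per group for 80% power at two-sided 5%, "if the rate under usual care is 15% or less and the true difference in proportions is at least 35" percentage points.

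**The concern.** The endpoint window is twice as long as the period in which controls are on usual care alone. By month 12 the control arm has had 6 months of usual care followed by up to 6 months in which the program was on offer. An intention-to-treat test of 12-month response then estimates the effect of starting now rather than about half a year later, which is not the effect named in the research question.

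Two things are at stake. First, if the program works, the delayed arm may partly catch up. The difference would shrink, and a null result could mean either that the program fails or that both arms benefited. Second, the sample size rests on a usual-care rate that no arm represents over the second half of the window.

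**Working it through.** **1. Reproduce the plan's figure.** Inputs from Sample size {14}: control rate p_C = 0.15, difference 0.35 (so program rate p_P = 0.50), n = 27 per arm, two-sided 5%, chi-square test.

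Power = Φ{[d√n − 1.96·√(2p̄(1−p̄))] / √(p_C(1−p_C) + p_P(1−p_P))}, with d = p_P − p_C and p̄ the mean of the two rates.

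With p̄ = 0.325: d√n = 0.35 × √27 = 1.8187; 1.96 × 0.6624 = 1.2983; denominator 0.6144. Then (1.8187 − 1.2983)/0.6144 = 0.847 and Φ(0.847) = 80.2%. The stated 27 per group reproduces. Exact enumeration of the uncorrected test gives 82.0%. The arithmetic is sound, but it describes a control arm at the usual-care rate.

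**2. Set the windows side by side (Table 2).**
- Illness-control markers, program arm: baseline, 3, 6 and 12 months.
- Illness-control markers, controls: baseline, 6, 9, 12 and 18 months.
- Shared post-baseline points: 6 and 12 months only. Month 6 is the only one that can precede control exposure.

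**3. Reading A: response is status at month 12.** Let f be the share of the 35-point effect that controls gain through their own program by month 12. The documents give no value for f, so it is an assumption shown as a range. Then p_C = 0.15 + 0.35f, against p_P = 0.50.

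| f | Control rate | Difference | Power, 27 per arm | Needed per arm for 80% |
|---|---|---|---|---|
| 0 | 15% | 35 points | 80.2% | 27 |
| 10% | 18.5% | 31.5 | 69.4% | 35 |
| 25% | 23.75% | 26.25 | 51.6% | 52 |
| 50% | 32.5% | 17.5 | 25.3% | 124 |
| 75% | 41.25% | 8.75 | 9.3% | 508 |

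Example for f = 50%: (0.175 × √27 − 1.96 × 0.6962)/0.6851 = (0.9093 − 1.3645)/0.6851 = −0.664, and Φ(−0.664) = 25.3%. Exact enumeration for f = 25%, 50% and 75% gives 52.1%, 24.3% and 8.7%. With all 60 recruited participants analysed (30 per arm), the formula gives 56%, 28% and 10%.

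**4. Reading B: response must be present at both 6 and 12 months.** A control can then respond only after improving by month 6 under usual care, so the control rate cannot exceed the 6-month usual-care rate. Keep 50% in the program arm.
- If the 6-month usual-care rate is at most 15%, power stays at 80% or more.
- If it were 20% and every such control kept the gain: (0.30 × √27 − 1.96 × 0.6745)/0.6403 = (1.5588 − 1.3220)/0.6403 = 0.370, which gives 64%.

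Under this reading the loss may be small or nil. Even so, controls hold any gain from month 6 to month 12 with the program available, so the comparison is still not with usual care alone.

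**5. Reading C: controls are judged over months 6 to 18**, as the 18-month control column in Table 2 might suggest. Both arms would then be judged on the program, and no usual-care comparator would be left.

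**The case against.** The strongest counter-argument is that the word sustained limits the damage. If improvement is needed at both shared visits, late exposure cannot create control responders but only help to keep them, and the steep power losses do not arise. This stands for the size of the loss, and the table under Reading A must be read as conditional. It does not restore the comparison, and the protocol does not say which visits count.

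Exposure may also be less than 6 months. Controls are invited at 6 months, and their start is tied to the next clinic visit, so uptake may be incomplete or late. This also stands. It supports saying that controls may partly catch up, and it leaves the 75% row as an illustration without support in the documents. The resulting mixture is of unknown size but is still a mixture.

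The separate analysis plan announced under Statistical methods {20a} could not settle this alone. Naming 6 months there would contradict the endpoint definition and the Table 1 footnote.

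A reader might go further in two ways that the documents do not support:
- **That the trial cannot answer its question at all.** Months 0 to 6 remain a randomized comparison of program with usual care, with markers in both arms. The fault lies in the endpoint definition.
- **That the protocol makes false claims about its comparator.** It says the design "allows for a comparison group at each time period and for analysis between each cluster" and that "This study has the capacity to demonstrate duration of effect with 12-month follow-up planned". The first is a general, referenced remark about the design and does not say that controls stay unexposed. The second does not say that duration will be shown by the randomized comparison, and within-arm follow-up fits its wording.

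**Conclusion.** Wrong as written. The 12-month endpoint, the 6-month crossover and analysis by randomized arm are all current text, and nothing limits the primary test to months 0 to 6. The primary comparison does not match the research question, and the 15% planning rate has no matching arm after month 6.

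The direction is likely toward no difference if the program works. The size is not fixed by the documents. It runs from little or no loss of power (improvement required at both visits, 6-month usual-care rate no more than 15%) to about 52%, 25% or 9% (status at month 12, with 25%, 50% or 75% of the effect gained by controls). All of these figures assume 50% response in the program arm. The mismatch itself does not depend on any of these assumptions.

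**What to change.** 1. Make the primary comparison response at 6 months from randomization, using the markers that Table 2 already schedules in both arms. For controls, use the last marker dated before the first Flinders session, because Table 2 also places their first delivery at 6 months.
2. Report 12- and 18-month results as secondary: early versus delayed start between arms, and durability within arm. State which visits must show improvement for a response to count as sustained.
3. Restate the 15% rate and the 35-point difference as 6-month assumptions and justify them afresh, since the documents give no 6-month rates. If they hold at 6 months, 27 per group (60 recruited) still gives 80.2% power. If they differ, restate the power.
4. Amend the protocol and the registry entry before anyone sees an outcome comparison by arm, and record that this was so. Recruitment began in December 2021 and the trial is open-label.

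**Cost.** No visits are added. The primary claim would cover 6 months only, the sustained element would become secondary, and the program would have less time to act. Markers come from the electronic medical record and controls start at a clinic visit, so some controls may lack a value dated before their first session.
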